# Electroacupuncture for slow flow/no-reflow phenomenon in patients with acute myocardial infarction undergoing percutaneous coronary intervention: protocol for a pilot randomized controlled trial

**DOI:** 10.3389/fcvm.2024.1401269

**Published:** 2024-06-18

**Keywords:** electroacupuncture, acute myocardial infarction, slow flow/no-reflow, protocol, randomized controlled trial (RCT) including age, gender, BMI, smoking history

## Abstract

**Background:**

Slow flow/no-reflow (SF-NR) during percutaneous coronary intervention (PCI) is associated with poor prognosis of patients with acute myocardial infarction (AMI). Currently, effective treatment is not available for SF-NR. Electroacupuncture (EA) has shown significant efficacy as an adjuvant therapy for many cardiovascular diseases by improving microcirculation and reducing ischemia-reperfusion injury. However, its effects on SF-NR in the AMI patients during PCI are not clear. This pilot trial aims to determine the efficacy of intraoperative EA in alleviating SF-NR in AMI patients undergoing PCI.

**Methods:**

This prospective, single-center, randomized controlled, pilot trial will recruit 60 AMI patients scheduled for PCI at the Yueyang Hospital of Integrated Traditional Chinese and Western Medicine, China. The patients will be randomized in a 1:1 ratio into the EA or the control groups. Patients in the control group will undergo standard PCI. Patients in the EA group will undergo intraoperative electroacupuncture while undergoing standard PCI. Incidence of SF-NR is the primary outcome for this study. This study will also assess secondary outcomes including cardiac biomarkers, inflammatory biomarkers, pain and anxiety scores, electrocardiography parameters, traditional Chinese medicine (TCM) symptom score, and major adverse cardiovascular and cerebrovascular events (MACCE). All the included patients will undergo laboratory tests including routine blood tests, levels of electrolytes, as well as liver and renal function tests. Patients will be followed up for 1 month after the procedure.

**Discussion:**

This pilot trial will provide evidence for the potential benefits of intraoperative EA in improving microvascular perfusion and preventing or alleviating SF-NR during PCI in patients with AMI. If proven effective, intraoperative EA will provide a new and effective strategy against SF-NR and provide evidence for subsequent multicenter trials.

**Clinical Trial Registration:**

ClinicalTrials.gov, identifier (ChiCTR2300072265). Registered on 8 June 2023.

## Introduction

1

Acute myocardial infarction (AMI) is a life-threatening condition caused by sudden coronary artery occlusion because of plaque rupture or thrombosis. Therefore, timely reopening of the infarct-related artery is necessary, for salvaging the jeopardized myocardium and restoring the blood flow (1). Percutaneous coronary intervention (PCI) is the primary treatment method for relieving the occluded coronary artery and is associated with minimal invasiveness and rapid recovery (2–4). Despite successful recanalization, 41% of the cases report insufficient blood flow that can lead to a severe complication called as slow flow/no reflow (SF-NR) (5, 6). Patients with SF-NR can develop severe complications, such as like ventricular arrhythmias, heart failure, and sudden death, all of which result in poor prognosis and negate the benefits of PCI in the AMI patients (7–9). SF-NR is associated with a five-fold increase in risk of myocardial infarction and a four-fold increase in the mortality rate (10).

The mechanisms causing SF-NR include microvascular embolization, *in situ* thrombosis, endothelial cell damage, microvascular spasms, and inflammation (11–15). Currently, there are no specific universal class I treatment strategies for alleviating SF-NR. Patients with SF-NR are treated with drugs such as vasodilators and glycoprotein IIb/IIIa antagonists, as well as mechanical treatments, including thrombus aspiration (16, 17). However, there is no definitive evidence that these treatments specifically target and alleviate SF-NR. These treatment methods often target only one causative factor and result in inconsistent and unstable effects. Moreover, most of the treatments are associated with significant adverse effects. For example, excessive use of tirofiban is associated with elevated bleeding risk (18), whereas improper thrombus aspiration causes complications such as thrombus dislocation (19). Therefore, there is an urgent need to discover safe and more effective treatment strategies for alleviating SF-NR.

Acupuncture demonstrates various biological effects, including autonomic nervous system regulation, anti-inflammatory properties, enhanced microcirculation, antioxidant activity, reduced lipid levels, and perioperative pain relief (20, 21). Therefore, it may be a promising strategy for addressing coronary microvascular dysfunction, injury, and obstruction following AMI, such as SF-NR. Firstly, it modulates sympathetic and parasympathetic balance, thereby attenuating sympathetic overactivity and enhancing parasympathetic tone, which may contribute to vasodilation and improved coronary microcirculation (22, 23). Secondly, acupuncture exhibits robust anti-inflammatory properties, as evidenced by its ability to downregulate pro-inflammatory cytokines and inhibit the activation of nuclear factor-kappa B (NF-κB), thus mitigating the inflammatory cascade implicated in microvascular injury post-MI (24). Thirdly, acupuncture exerts antioxidant effects by bolstering endogenous antioxidant defenses and scavenging reactive oxygen species, thereby mitigating oxidative stress-induced damage to endothelial cells and preserving microvascular integrity. Notably, EA has been shown to modulate endothelial function, promoting endothelial nitric oxide synthase (eNOS) activity and nitric oxide (NO) production, pivotal mediators of vasodilation and endothelial homeostasis, thereby counteracting endothelial dysfunction associated with MI-induced microvascular impairment (25, 26). Therefore, acupuncture may potentially prevent SF-NR during PCI by reducing endothelial cell damage. Fourthly, acupuncture holds promise in mitigating microvascular spasm and obstruction by virtue of its vasodilatory effects and modulation of vascular smooth muscle tone (27). This is further corroborated by emerging evidence suggesting that acupuncture may regulate the renin-angiotensin-aldosterone system (RAAS), a key regulator of vascular tone and remodeling, thereby conferring vasoprotective effects and attenuating microvascular dysfunction post-MI (28). Furthermore, acupuncture has been shown to stimulate the release of endogenous opioids and neuropeptides, including β-endorphin and substance P, which contribute to pain relief and myocardial protection (29, 30). Additionally, PCI primarily targets large and medium-sized coronary vessels with stenosis but is not effective in treating thin or small-diameter vessels (31). Acupuncture addresses this limitation as an economical and non-invasive option for the treatment of blood flow issues in smaller blood vessels or complex or risky needle insertion situations. Acupuncture is also a viable option for patients seeking to avoid the side effects of drugs (32). Moreover, acupuncture is one of the earliest therapies for emergency treatment in traditional Chinese medicine (TCM) according to ancient classics. The clinical spectrum of acupuncture includes 16 categories with 461 types of human diseases, of which 26% were acute diseases (33). Acupuncture, particularly electroacupuncture (EA), shows significant clinical benefits. EA is a safe and effective intervention that is easier to standardize, more controllable than manual acupuncture, and provides prolonged stimulation, precise intensity control, and enhanced acupuncture sensation (34, 35). Therefore, combinatorial therapy with EA and PCI is a promising strategy for enhancing clinical outcomes, optimizing coronary blood flow, and improving patient prognosis.

Previous reports have suggested that acupuncture may be effective in preventing or alleviating SF-NR. However, it is not known whether electroacupuncture is effective in preventing or alleviating SF-NR in AMI patients undergo PCI, and high-quality randomized-controlled clinical trials (RCTs) are urgently necessary to investigate its efficacy and safety. Therefore, in this pilot RCT, we aim to investigate the potential benefits of intraoperative EA in reducing SF-NR during PCI in the AMI patients. The findings of this study are expected to lay the foundation for subsequent multicenter trials to establish the clinical safety and efficacy of intraoperative electroacupuncture as a novel strategy for managing SF-NR in AMI patients during PCI.

## Methods and analysis

2

### Study design

2.1

This pilot trial will adopt a single-center, blinded, randomized controlled design to determine the efficacy of intraoperative EA in preventing or reducing the incidence of SF-NR in patients with AMI undergoing PCI with standard PCI as control. The trial will follow the Chinese AMI management guidelines and the Declaration of Helsinki. This study has been approved by the Ethics Committee [Approval No. 2023-090-01]. All the study participants will be screened according to the inclusion and exclusion criteria. Finally, sixty eligible patients will be recruited and randomly assigned in a 1:1 ratio to either the EA group or the control group after obtaining informed consent. Patients in the acupuncture group will receive electroacupuncture during the standard PCI procedure, whereas patients in the control group will only receive the standard PCI procedure. The trial period will include the treatment duration from the time of hospital admission to the completion of PCI and a one-month follow-up period.

The protocol will be designed in compliance with the Standard Protocol Items for Randomized Trials (SPIRIT). The SPIRIT checklist is included in the Supplementary Appendix. The trial flow chart is shown in Figure 1. The study design schedule is shown in Table 1.

**Figure 1 F1:**
[figure not shown]
Flow chart of the trial.

**Table 1 T1:** Study design schedule.

Study period	Treatment period			Follow-up period		
Timepoint	Preoperative PCI	Intraoperative PCI	Postoperative PCI	Postoperative		
				12 h	72 h	1 M
Demographic data^a^	√					
Routine drug treatment	√	** **	√	** **	** **	** **
Acupuncture (left Neiguan with Ximen)	** **	√	** **	** **	** **	** **
Incidence of Slow flow/no-reflow (TIMI and CTFC)	** **	√	** **	** **	** **	** **
Changes in cardiac biomarkers^b^	√	** **	** **	√	√	** **
Inflammatory markers^c^	√	** **	** **	√		** **
Pain score (NRS)	√	** **	√	√	** **	** **
VAS-A scores	√		√	√	** **	** **
Electrocardiogram	√	** **	√	√	** **	** **
TCM symptom score	√	** **	** **	** **	√	** **
MACCE	** **	** **	** **	** **	** **	√
Adverse events	√	√	√	√	√	√
Safety assessments^d^	√	** **	** **	** **	√	

^a^
Including age, gender, BMI, smoking history, medical history, and symptom duration.

^b^
Including cTnI, Myo, CK-MB, NT-proBNP.

^c^
Including leukocytes, neutrophils, lymphocytes, and Hs-CRP.

^d^
Including blood routine, electrolytes, liver and renal functions.

### Participants and recruitment

2.2

The study is scheduled to be conducted from August 2023 to June 2025 at Yueyang Hospital affiliated with Shanghai University of Traditional Chinese Medicine. Sixty AMI patients requiring PCI will be recruited from the Emergency Department and undergo PCI in the cardiac catheterization laboratory. The diagnostic criteria for inclusion will be based on follow the Fourth Universal Definition of Myocardial Infarction (2018) (36). The investigator will describe the study details, including the purpose, benefits, and potential risks of the study to the patients. Patients agreeing to voluntarily participate in this study will need to provide signed informed consent, undergo eligibility assessment, and provide demographic information. The intervention and follow-up will adhere to the protocol. Participants will be allowed to withdraw without penalty.

### Inclusion criteria

2.3

(1)Patient age between 18 and 80, regardless of gender.(2)Patients meet the diagnostic criteria for AMI and schedule for PCI.(3)Patients provide informed consent to participate.

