### Exclusion criteria

2.4

(1)Patients with severe liver, kidney, and hematopoietic system impairments (e.g., serum alanine aminotransferase >3 times the normal value or serum creatinine ≥265 μmol/L).(2)Patients unable to cooperate or complete the PCI procedure because of alcoholism or cognitive dysfunction.(3)Patients with severe cardiac complications, including cardiogenic shock.(4)Patients unsuitable for acupuncture because of skin damage or infection.(5)Patients who have undergone surgery in the last four weeks and have a risk of bleeding, during the procedure, or patients who are participating in other clinical trials.

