### Quality control and assurance

2.14

The trial protocol has undergone rigorous review by the experts in acupuncture, cardiovascular medicine, statistics, and methodology. Investigators will be identified post-eligibility screening and a consistent staff will be maintained throughout the study. All the researchers, including acupuncturists, evaluators, and statisticians will receive pre-initiation training for consistently implementing the protocols. Regular meetings will be held to review the study progress, address any issues, and ensure protocol adherence. Laboratory tests will follow standard operating requirements with prompt explanations for any changes during the study. Licensed acupuncturists with over two years of experience will administer acupuncture treatment exclusively while avoiding other therapies such as acupressure and moxibustion. Furthermore, experts will supervise and guide the operators throughout the procedures, and promptly address any issues that may arise and ensure the smooth progression of surgeries. High patient compliance will be ensured because of the nature of the emergency surgery, and will be supported by drug counting, regular checks, compensation, and health education. The reasons for dropouts and withdrawals, if any, will be carefully documented. While improving patient compliance, researchers will strictly limit the inclusion criteria and use fully randomized, blinded, and concealed assignments. Efficacy and safety indicators will be evaluated and documented by independent assessors who are unaware of the group assignments. Medical records will be strictly confidential, with anonymous data processing. The data will be accessible only to the authorized researchers and the sponsor representatives. Throughout the trial, all the investigators will adhere to strict confidentiality policies.

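### Cardiac biomarkers are timed from PCI and compared by unadjusted tests although symptom duration is recorded: adjust for it, and leave the all-comer entry rule as it is

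*Protocol article*

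**What the plan says.** **Entry.** The second of three inclusion criteria (section 2.3) is "Patients meet the diagnostic criteria for AMI and schedule for PCI". The five exclusions (section 2.4) do not mention time from onset. Section 2.2 adds the diagnostic definition and the source of patients: "Sixty AMI patients requiring PCI will be recruited from the Emergency Department".

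**Setting.** The Introduction states that "timely reopening of the infarct-related artery is necessary, for salvaging the jeopardized myocardium". Section 2.14 says "High patient compliance will be ensured because of the nature of the emergency surgery".

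**Timing of the biomarkers.** Table 1 places the cardiac biomarkers (cTnI, Myo, CK-MB, NT-proBNP) before PCI and at 12 h and 72 h after it, and labels the outcome as a change.

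**Symptom duration.** It is a baseline item, under Table 1 footnote a: "Including age, gender, BMI, smoking history, medical history, and symptom duration". Section 2.6 names gender, age and STEMI status as stratification variables, as examples. Symptom duration is not among them.

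**Analysis.** Section 2.15 prescribes independent-sample t-tests between groups for normally distributed data, non-parametric tests between groups otherwise, and paired t-tests within groups. It names no covariate.

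**The concern.** The sampling clock starts at PCI, while the infarction started at symptom onset. Patients enter at any interval between the two. For a marker that rises and then falls after infarction, a pre-PCI sample taken early lies on the rise and one taken late lies on the fall. The change to 12 h or 72 h can then differ in size, and even in sign, between two patients whom the intervention did not affect.

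Two things are at stake. Time since onset adds spread to every between-group biomarker comparison, and in groups of 25 to 30 it can also be unevenly distributed by chance. And a within-group paired test will register the natural course of the marker, which may be mistaken for an effect of electroacupuncture.

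**Working it through.** **1. Numbers per arm.** Section 2.12 takes 25 per group and adds 20%: 25 × 1.20 = 30 per group, 60 in total, as stated. There is no power calculation to reproduce. The calculations below use 25 to 30 per arm.

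**2. What each test measures when there is no treatment effect.** Let T be the hours from onset to PCI, and g(T, h) the expected log marker h hours after a standard PCI. The change at 12 h is g(T, 12) − g(T, 0), which depends on T.
- *Between arms:* T has the same distribution in both arms by randomisation, so the expected difference is 0. There is no bias.
- *Within an arm:* the paired test asks whether the mean of g(T, 12) − g(T, 0) is 0. There is no reason for it to be 0, whether or not electroacupuncture works.

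The documents do not describe the release curve. That cTnI, Myo and CK-MB rise and then fall is taken here as general knowledge.

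**3. Cost in precision.** If T explains a share R² of the variance, the unadjusted standard error exceeds the adjusted one by the factor 1/√(1 − R²). The documents give no R², so a range is assumed. The detectable difference, in unadjusted SD units at 80% power and two-sided 0.05 (the article does not state sidedness), is (1.960 + 0.842) × √(2/n) × √(1 − R²).

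| Assumed R² | SE factor | Detectable, n = 30 per arm | Detectable, n = 25 per arm |
|---|---|---|---|
| 0 | 1.000 | 0.72 | 0.79 |
| 0.10 | 1.054 | 0.69 | 0.75 |
| 0.25 | 1.155 | 0.63 | 0.69 |
| 0.40 | 1.291 | 0.56 | 0.61 |

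At R² = 0.10 to 0.40, an unadjusted analysis of 60 patients is worth an adjusted one of 60 × (1 − R²) = 54 to 36.

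**4. Chance imbalance.** For a continuous T, the standardised difference between arms has standard error √(2/n), which is 0.258 for n = 30 and 0.283 for n = 25. It exceeds 0.25 in 33% of randomisations (38% for n = 25) and 0.5 in 5% (8% for n = 25).

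As a yes/no split with 30 per arm and simple 1:1 allocation (hypergeometric), the arms differ by at least 20 percentage points in late presenters in 10%, 16% and 20% of randomisations if 20%, 30% and 50% of patients are late. Those shares are assumed. The calculation ignores stratification by STEMI, so it overstates the risk to the extent that lateness follows STEMI status.

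Steps 3 and 4 describe the same source of variation and should not be added together. The unadjusted standard error already allows for the imbalance.

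**The case against.** **The entry rule contradicts the rationale.** A reader might infer this from the stress on prompt reopening and emergency surgery. The documents do not support it. The Introduction describes why AMI needs treatment; it does not confine the trial to early presenters. The Discussion speaks of a varied AMI population, and stratifying on STEMI status shows that a mixed sample was planned. An entry window added now, with recruitment ongoing (section 4), would also split a 60-patient pilot into two eligibility periods.

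**The arms' comparison is biased.** A reader might infer this too. Step 2 shows that it is not, in expectation.

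**STEMI stratification already handles it.** This stands in part. It balances the contrast between STEMI and non-STEMI patients, but not the spread of timing within each. Recruitment through the Emergency Department may shorten some delays, but it sets no limit.

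**The primary outcome is at risk.** The rise-and-fall argument concerns biomarkers, which are secondary. Nothing in the documents shows how far time since onset affects SF-NR. Nor would biomarker variance size a later trial whose endpoint is SF-NR incidence.

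**Covariates belong in the analysis plan, which is not shown.** This is fair as to detail. But section 2.15 does not leave the tests open: it states them, and they are unadjusted. If the analysis plan already adjusts for symptom duration, section 2.15 should be brought into line with it.

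**Conclusion.** The point holds as one of precision and interpretation for the cardiac biomarkers. The stated tests ignore a recorded baseline value on which those outcomes plausibly depend. Standard errors are then about 5% to 29% larger than needed if time since onset explains 10% to 40% of the variance. That range is assumed, and so is the rise and fall of the markers. In a model that already holds the pre-PCI value and STEMI status, the further gain from time since onset could be smaller. Within-group paired changes cannot be read as treatment effects, whatever the value of R².

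The absence of an onset-to-PCI limit is not an error, and no bias in the randomised comparison is shown. The point is of modest weight: the outcomes are secondary and the trial is a pilot, but the correction is cheap.

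**What to change.** In section 2.15, for the cardiac biomarkers:

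1. Replace the unadjusted between-group tests by an ANCOVA at 12 h and at 72 h: log post-PCI value on arm, log pre-PCI value, log onset-to-PCI time and STEMI status. Report the arm effect as a ratio of geometric means with its 95% confidence interval.
2. State that onset-to-PCI time comes from the recorded symptom duration, and to which moment that duration runs. Table 1 does not say.
3. Treat within-group paired tests as descriptive, and draw no conclusion on efficacy from them.
4. Tabulate symptom duration by arm.
5. Label any analysis of SF-NR adjusted for symptom duration as supportive.

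Eligibility stays as it is.

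**Cost.** A few lines of analysis text, a little more analysis work and no new data. Against the t-test the model has three further coefficients, so residual degrees of freedom fall from 58 to 55 with 60 patients, or from 48 to 45 with 50. Section 2.7 keeps the statisticians blinded until the analysis is complete, so the change can be fixed before they know the allocation.

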### Exclusion criteria

2.4

(1)Patients with severe liver, kidney, and hematopoietic system impairments (e.g., serum alanine aminotransferase >3 times the normal value or serum creatinine ≥265 μmol/L).(2)Patients unable to cooperate or complete the PCI procedure because of alcoholism or cognitive dysfunction.(3)Patients with severe cardiac complications, including cardiogenic shock.(4)Patients unsuitable for acupuncture because of skin damage or infection.(5)Patients who have undergone surgery in the last four weeks and have a risk of bleeding, during the procedure, or patients who are participating in other clinical trials.

### Termination and dropout of trial patients

2.5

(1)Patients with poor protocol compliance and failing to receive treatment.(2)Patients with incomplete medical records that impact evaluating the efficacy.(3)Voluntary withdrawal by the patient.(4)Adverse events (AEs) that render the participant unfit to continue.(5)Patients considered as not suitable to continue by the researcher.

